## Abstract

**Background**: Paroxysmal atrial fibrillation (PAF) presents significant challenges in management due to its unpredictable recurrence and associated complications. Current prognostic tools lack precision in predicting PAF outcomes, highlighting the need for a comprehensive approach integrating multiple diagnostic modalities. **Methods:** The PLACEBO pilot study is a prospective observational investigation enrolling 80 adults with PAF from a tertiary hospital. Baseline assessments include cardiopulmonary exercise testing (CPET), a complete echocardiographic evaluation, 24-h ambulatory electrocardiographic monitoring, and plasma biomarker analysis. Participants will be followed for 12 months, with the primary outcome being AF recurrence. Secondary outcomes include cardiovascular events and other clinical indicators relevant to disease progression. **Results:** The study will assess the feasibility of integrating CPET parameters, echocardiographic indices, and plasma biomarkers into clinical practice for prognostic evaluation. Data analysis will focus on identifying potential associations between these modalities and PAF recurrence, contributing to improved risk stratification. **Conclusions**: By integrating CPET, echocardiographic parameters, and plasma biomarkers, the PLACEBO pilot study aims to enhance risk stratification and improve the prognostic assessment of patients with PAF. The findings from this study may pave the way for future research, ultimately contributing to the development of personalized management strategies.

## 1. Introduction

Atrial fibrillation (AF) is the most common cardiac arrhythmia encountered in the Western world, constituting a significant burden on patients and healthcare systems [1]. AF is characterized by an irregular and often rapid cardiac rhythm and is associated with significant morbidity and mortality, including increased risks of stroke, heart failure, and all-cause mortality [2]. Despite advancements in the management and of AF and in therapeutic approaches, the prevalence of AF continues to rise and is accompanied by an increase in the incidence of major adverse cardiovascular events (MACE), underscoring the need for novel, patient-centered management strategies [3].

Paroxysmal atrial fibrillation (PAF), a subtype of AF, is defined by self-terminating episodes that usually last less than 7 days [4]. Despite its transient nature, PAF poses substantial challenges in clinical management due to its multifactorial basis, unpredictable recurrence, and associated complications [5,6]. The prognosis of PAF varies depending on several factors, including the frequency and duration of episodes, the presence of underlying cardiovascular conditions, and individual patient characteristics [7]. While PAF generally carries a lower risk of adverse outcomes such as stroke compared to persistent or permanent AF, it still necessitates high awareness and effective management to mitigate potential risks and optimize long-term outcomes [8]. Understanding the natural history and prognostic indicators specific to PAF is crucial for tailoring therapeutic approaches aimed at rhythm control, reducing symptoms, and minimizing the risk of MACE in affected individuals.

Cardiopulmonary exercise testing (CPET) is a valuable tool in our clinical practice, providing comprehensive information about the cardiovascular, respiratory, and musculoskeletal response to exercise [9,10]. CPET plays a crucial role in predicting future cardiac events in various conditions, including AF [11]. However, data regarding the precise relationship between cardiorespiratory fitness and AF prognosis are conflicting, with some studies suggesting that higher fitness levels increase AF risk and others indicating a protective effect [12,13]. Recent advancements in CPET have opened new avenues for the prognostic evaluation of AF [14].

In the same line, novel echocardiographic indices and plasma biomarkers have emerged as promising tools for assessing cardiac function and inflammation, critical components of the pathophysiology of AF [15,16,17,18]. These advancements highlight the need for an integrative approach to AF prognostication, incorporating CPET, echocardiography, and biomarkers to address current knowledge gaps.

We set out to design a pilot study with the aim of integrating the aforementioned innovative diagnostic approaches in AF management to explore their feasibility and potential utility for the prediction of arrhythmic recurrences. Therefore, the PLACEBO trial serves as an exploratory feasibility study to evaluate the potential significance of these diagnostic modalities in predicting AF recurrence and related adverse outcomes. By providing initial insights, the trial seeks to identify promising predictors and generate hypotheses that could guide future, larger-scale studies aimed at enhancing predictive accuracy and supporting more personalized management strategies for patients with PAF.

## 2. Methods

### 2.1. Study Design

The PLACEBO (“ParoxysmaL Atrial fibrillation prognosis based on Cardiopulmonary Exercise test data and novel echocardiographic and plasma BiOchemical indices”) trial is a pilot, prospective, observational cohort study designed to explore the feasibility of integrating CPET data, novel echocardiographic indices, and plasma biochemical markers in consecutive patients with PAF for the prediction of AF recurrences. As this is a feasibility study, no specific treatment interventions were prescribed as part of the study protocol. Instead, the study aims to identify potential signals and generate hypotheses for future larger-scale investigations.

The sample size of 80 participants was chosen pragmatically, based on the feasibility of recruitment and data collection within the study’s timeframe and resources. Formal sample-size calculations were not performed, as the primary aim of the study is to assess the feasibility of the proposed methodology and to explore potential predictors of AF recurrence, rather than to test specific hypotheses. This approach aligns with the exploratory nature of pilot studies, aiming to provide preliminary insights into the utility of these diagnostic modalities and establish a basis for future, larger-scale studies.

The study is being conducted at Ippokratio General Hospital in Thessaloniki, Greece. The protocol of the trial is registered at ClinicalTrials.gov (Identifier: NCT05246423) and has been reviewed and approved by the Institutional Review Board (IRB) of Ippokratio General Hospital, as well as by the Aristotle University of Thessaloniki Ethics Committee. Written informed consent was obtained from all participants prior to any study-related procedures. The study is being conducted in accordance with the Declaration of Helsinki and Good Clinical Practice guidelines.

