### 2.2. Participants

Participants in the study were adults aged 18 years and older, diagnosed with PAF, and in sinus rhythm at the time of baseline evaluation. Eligible participants were required to undergo CPET and comply with follow-up requirements.

PAF was defined according to the ESC 2020 and 2024 Guidelines as AF episodes that terminate spontaneously or with an intervention within 7 days, typically within 48 h [4,19]. Patients with persistent or permanent AF were excluded to maintain a homogeneous study population. To ensure accurate classification, all patients had a documented time of AF onset, as reported from one of the following sources:Hospitalization with a recorded AF episode and documented termination.Outpatient or patient visit to the Emergency Department with a definite AF onset time, either self-reported or confirmed via surface electrocardiogram (ECG) or 24-h ECG Holter monitoring.AF episode terminated in-hospital, either spontaneously, pharmacologically, or electrically.

Additionally, all participants underwent 24-h ambulatory ECG Holter monitoring at baseline to confirm sinus rhythm and assess AF burden. Medical records and prior ECG documentation were reviewed to validate AF classification and exclude cases of persistent AF.

To assess the duration of AF, data were collected regarding the time since the first documented AF diagnosis based on medical records and patient history. While the exact onset date was not necessarily available, disease duration was recorded as a key variable to assess AF burden and progression.

The inclusion criteria were meeting these conditions and being capable of providing written informed consent. The exclusion criteria consisted of structural cardiomyopathy, congenital heart disease, permanent AF, recent acute coronary syndrome (within the last month), heart failure (HF) with reduced ejection fraction, end-stage renal disease, autoimmune diseases, active malignancies, uncontrolled thyroid disease, recent surgery (within the last 2 months), poor echocardiographic windows, uncontrolled systemic hypertension, prior catheter ablation for AF, and pregnancy. Patients unable to comply with the study schedule or provide informed consent were also excluded.

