### 2.4. Outcome Measures

The primary outcome measure is the recurrence of AF within 12 months from enrollment. This will be determined based on available electronic data and through detailed patient interviews during follow-up sessions. Secondary outcome measures will include a variety of clinical and diagnostic indicators, which will be used to evaluate the overall cardiovascular health of and AF progression in participants. These measures will encompass AF-related hospitalizations, types of cardioversions performed, the total burden of premature atrial and ventricular contractions, and episodes of AF recorded during 24-h ECG ambulatory Holter monitoring. Other ECG parameters such as microvolt TWA and HRV indices will also be assessed.

Additional secondary measures will include key performance metrics from CPET such as peak VO_2_ and VE/VCO_2_ slope, as well as echocardiographic indices like LA strain and LV GLS. Plasma biomarkers such as galectin-3, homocysteine, BNP, and hs-cTnI will also be measured to explore their potential role in predicting AF progression. The time to the first recurrence of AF will also be tracked, which may provide valuable insights into factors that could influence the recurrence of AF.

This study aims to assess the feasibility of monitoring and correlating these measures as potential predictors of AF recurrence, ultimately setting the stage for further validation in a larger, more definitive study.

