### Study Limitations

This pilot study has a series of limitations that should be considered when interpreting the results. One key limitation is the small sample size, which, typical for pilot studies, limits the statistical power and generalizability of the findings. Consequently, the results should be viewed as exploratory and cannot be conclusively applied to the broader population of patients with PAF.

Additionally, the study lacks an independent validation cohort, which limits the ability to externally validate any potential predictive models derived from this dataset. However, as a feasibility study, the primary objective is to identify potential signals and generate hypotheses, rather than to develop definitive prediction models at this stage. Future large-scale studies will be necessary to validate these findings in independent cohorts and refine predictive models before clinical implementation.

Another limitation is the relatively short 12-month follow-up period, which may not be sufficient to capture the long-term dynamics of AF recurrence and other cardiovascular outcomes, with longer-term studies being necessary to better understand the chronicity of these events.

Despite these limitations, the PLACEBO pilot study serves as an important first step toward evaluating the feasibility of a multifaceted approach to predicting AF recurrence, setting the scene for future, larger-scale studies to confirm and refine these findings.

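### The feasibility half of the stated primary aim has no outcome or analysis, and the eligibility rules would make baseline completion among the 80 enrolled overstate feasibility in consecutive PAF patients

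*Protocol article*

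**What the plan says.** **Aim.** Section 2.1 of the Protocol article gives a two-part primary aim. The first part is that "the primary aim of the study is to assess the feasibility of the proposed methodology"; the second, in the same sentence, is exploration of what might predict AF recurrence. The same sentence uses this aim to explain why no formal calculation was made, and the size is described as follows: "The sample size of 80 participants was chosen pragmatically, based on the feasibility of recruitment and data collection". The Abstract also promises an assessment of whether the tests can feasibly be integrated into clinical practice.

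**Objective, worded again.** Study Limitations states that "as a feasibility study, the primary objective is to identify potential signals and generate hypotheses".

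**Outcomes.** Section 2.4 states: "The primary outcome measure is the recurrence of AF within 12 months from enrollment". The secondary outcomes are AF hospitalizations, cardioversion types, Holter measures, CPET metrics, echocardiographic indices, biomarkers and time to first recurrence. The section closes with feasibility as an aim, without a measure attached: "This study aims to assess the feasibility of monitoring and correlating these measures as potential predictors of AF recurrence".

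**Eligibility.** Section 2.1 describes a consecutive series of PAF patients. Section 2.2 adds: "Eligible participants were required to undergo CPET and comply with follow-up requirements". It lists poor echocardiographic windows among the exclusions, and ends: "Patients unable to comply with the study schedule or provide informed consent were also excluded".

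**The concern.** A pilot that names feasibility in its primary aim, and relies on it to justify its size, should say what it will measure to judge feasibility. This article lists its primary and secondary outcomes, and none of them does so. The gap is therefore a mismatch between two things the article states, not a detail left to a fuller document.

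Eligibility adds a second problem. Inability to do CPET, inadequate windows and inability to attend are main ways in which the combined work-up would fail in practice. Patients with these problems leave before the denominator is formed. A completion rate among the enrolled would then describe preselected patients, while the design section speaks of consecutive ones.

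At stake is the claim that the work-up is feasible. Followed as written, the plan produces associations with AF recurrence and no feasibility result, so that claim would be unsupported when the larger study is proposed.

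**Working it through.** **1. The plan's own figure.** The sample size of 80 is pragmatic by declaration, with no alpha, power or effect size. There is nothing to reproduce or refute.

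**2. Aim against outcome and analysis.**

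| Part of the aim (2.1) | Matching outcome (2.4) | Matching analysis (2.5) |
|---|---|---|
| Explore predictors of AF recurrence | AF recurrence within 12 months; time to first recurrence | Linear, logistic and Cox models; decision trees possible |
| Assess feasibility of the methodology | None: no recruitment, test-completion, analysable-data or retention measure | None: missing data are imputed and compared with complete cases, but completeness is not a stated result |

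The first row is served. The second is empty. Study Limitations then gives signal finding alone as the primary objective, which matches the first row only.

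**3. Where eligibility acts.** From 2.2, 2.3.1 and 2.3.2:

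- Selected on before enrolment: undergoing CPET, adequate echocardiographic windows, judged ability to keep the schedule.
- Not guaranteed by eligibility: CPET quality, usable Holter indices, assayable stored plasma for the five biomarkers, attendance at the repeat echocardiogram and Holter, known 12-month AF status.

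The upward bias therefore falls mainly on baseline CPET and echocardiography. The other components can still vary among the 80 and could be measured.

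**4. Is 80 enough to estimate a feasibility proportion?** The exact (Clopper-Pearson) 95% interval for x of n has lower limit Beta quantile (0.025; x, n - x + 1) and upper limit Beta quantile (0.975; x + 1, n - x). With n = 80:

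- 56/80 = 70%: 58.7-79.7%
- 64/80 = 80%: 69.6-88.1%
- 72/80 = 90%: 81.2-95.6%
- 76/80 = 95%: 87.7-98.6%

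The precision is moderate and usable.

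**5. How far could the denominator move the figure?** Let f be the share of otherwise eligible patients removed because CPET, windows or schedule were not feasible. The article gives no value, so f is an assumption. The number needed to enrol 80 is n = 80/(1 - f), rounded up. Suppose all 80 complete. The enrolled-only result is 80/80 = 100% (95.5-100%) whatever f is. With the removed patients counted:

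| Assumed f | n | 80/n | Exact 95% CI |
|---|---|---|---|
| 5% | 85 | 94.1% | 86.8-98.1% |
| 10% | 89 | 89.9% | 81.7-95.3% |
| 20% | 100 | 80.0% | 70.8-87.3% |
| 30% | 115 | 69.6% | 60.3-77.8% |

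The enrolled data cannot show which row applies; only screening records can.

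**The case against.** The strongest reply has four parts.

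- **The aim has two halves.** AF recurrence is the natural outcome for exploring predictors, and Study Limitations makes signal finding the primary objective. This stands. A reader might infer that the study cannot answer its primary question at all; the text supports that only for the feasibility half.
- **The article uses feasibility loosely.** Sections 2.1, 2.3.2 and 2.4 tie it largely to correlating measurements with recurrence, so the association analyses bear on it. This stands in part. But 2.1 also speaks of the feasibility of the methodology, and the Abstract of integration into clinical practice. Association models do not show whether the tests can be completed and analysed.
- **Completion is not fixed by eligibility.** A reader might infer that it is close to 100% by construction. That fits at most baseline CPET performance and echocardiographic windows. Section 2.5 plans for missing data, so the authors expect some incompleteness among the enrolled.
- **Screening logs, completeness tables and progression thresholds may sit in the full protocol.** This stands: their absence from an article is no fault, and the point does not rest on it. It rests on the outcome list not matching the aim.

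A reader might also infer that a larger study would have no data behind it. That goes too far, since the plan yields recurrence rates, predictor distributions, missingness and candidate associations.

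**Conclusion.** The point holds for the feasibility half of the primary aim. That half has no matching outcome or analysis, the primary objective is worded differently in 2.1 and Study Limitations, and the eligibility rules would bias baseline feasibility upward if it were read as applying to consecutive PAF patients.

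The direction of the bias follows from the text; its size does not. The range of about 94% down to 70% rests on an assumed 5-30% screened out and on all 80 completing, and should not be read as an estimate of true completion. Sample size is not the obstacle.

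The documents do not require AF recurrence to be demoted. It fits the predictor half, the study is registered and the baseline work is described as done, so changing the primary outcome now would raise a problem of its own. Go/no-go thresholds are debatable and are not needed to resolve the mismatch.

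**What to change.** 1. State one primary objective, in the same words, in 2.1 and Study Limitations.
2. Keep AF recurrence within 12 months as the primary clinical outcome, for the predictor-exploration half.
3. Add named feasibility outcomes in 2.4 for the other half, each with an exact 95% CI: the proportions of enrolled patients with analysable CPET, with analysable LA and LV strain, with analysable Holter, and with all five biomarkers; the proportion with completed follow-up echocardiogram and Holter; and the proportion with 12-month AF status known.
4. Where screening records were kept, report the number of consecutive PAF patients screened and the counts excluded for CPET inability, echocardiographic windows or schedule. Give baseline feasibility on that denominator as well.
5. If such records do not exist, limit any feasibility conclusion to patients preselected as able to complete the work-up.

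The cost is slightly more tabulation and a less favourable feasibility figure. No new patients or tests are needed, and the recurrence analysis is unchanged.

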### 2.2. Participants

Participants in the study were adults aged 18 years and older, diagnosed with PAF, and in sinus rhythm at the time of baseline evaluation. Eligible participants were required to undergo CPET and comply with follow-up requirements.

PAF was defined according to the ESC 2020 and 2024 Guidelines as AF episodes that terminate spontaneously or with an intervention within 7 days, typically within 48 h [4,19]. Patients with persistent or permanent AF were excluded to maintain a homogeneous study population. To ensure accurate classification, all patients had a documented time of AF onset, as reported from one of the following sources:Hospitalization with a recorded AF episode and documented termination.Outpatient or patient visit to the Emergency Department with a definite AF onset time, either self-reported or confirmed via surface electrocardiogram (ECG) or 24-h ECG Holter monitoring.AF episode terminated in-hospital, either spontaneously, pharmacologically, or electrically.

Additionally, all participants underwent 24-h ambulatory ECG Holter monitoring at baseline to confirm sinus rhythm and assess AF burden. Medical records and prior ECG documentation were reviewed to validate AF classification and exclude cases of persistent AF.

To assess the duration of AF, data were collected regarding the time since the first documented AF diagnosis based on medical records and patient history. While the exact onset date was not necessarily available, disease duration was recorded as a key variable to assess AF burden and progression.

The inclusion criteria were meeting these conditions and being capable of providing written informed consent. The exclusion criteria consisted of structural cardiomyopathy, congenital heart disease, permanent AF, recent acute coronary syndrome (within the last month), heart failure (HF) with reduced ejection fraction, end-stage renal disease, autoimmune diseases, active malignancies, uncontrolled thyroid disease, recent surgery (within the last 2 months), poor echocardiographic windows, uncontrolled systemic hypertension, prior catheter ablation for AF, and pregnancy. Patients unable to comply with the study schedule or provide informed consent were also excluded.

### 2.3. Data Collection

#### 2.3.1. Baseline

Participants underwent a comprehensive assessment at baseline, which included the collection of demographic data and full medical history, CPET, full transthoracic echocardiographic assessment, 24-h ECG ambulatory Holter monitoring, and measurement of plasma biomarkers.

Demographics and baseline characteristics: The baseline characteristics of the study population were collected and will be summarized using descriptive statistics. Demographic data (age, gender, body mass index), clinical characteristics (history of cardiovascular diseases, medication use), and baseline values of CPET parameters, echocardiographic indices, and plasma biomarkers will be presented. Continuous variables will be expressed as means and standard deviations or medians and interquartile ranges, depending on their distribution. Categorical variables will be presented as frequencies and percentages.CPET: The study participants underwent a full CPET workup, including a symptom-limited exercise test on a cycle ergometer, with continuous 12-lead ECG monitoring of cardiac rhythm, measurement of respiratory gases, and assessment of heart rate (HR) and arterial blood pressure. CPET allows for the measurement of over 50 parameters, each of which holds prognostic significance across a wide range of cardiovascular conditions. The primary measures obtained from CPET include peak oxygen uptake (peak VO_2_) and the minute ventilation/carbon dioxide production slope (VE/VCO_2_ slope), indices whose prognostic role has already been established in HF. Gas-exchange physics in patients with AF have been an item of interest for decades; nevertheless, the exact role of CPET in determining the AF prognosis has not yet been established.Transthoracic echocardiography: A standard, complete transthoracic echocardiographic study was performed in all patients under stable hemodynamic conditions. All echocardiograms were conducted by a single experienced cardiologist using a GE Vivid E95 ultrasound system (GE Healthcare, Chicago, IL, USA). A series of echocardiographic parameters were obtained, including the dimensions and functionality of the left ventricle (LV) [volume, mass, dimensions, left ventricular ejection fraction (LVEF) as measured using Simpson’s method, and global longitudinal strain (GLS)], diastolic indices of the LV (E/A, E/E’ ratio, mean TDI), and LA indices, including dimensions, volume, ejection fraction, and LA strain components (reservoir, conduit, and contractile strain). Pulmonary artery systolic pressure (PASP) was also assessed as a measure of pulmonary hemodynamics. Additionally, right atrial (RA) size and right ventricular (RV) dimensions, volume, and function were recorded to provide further insight into atrial−ventricular interactions. All measurements were conducted in accordance with the latest guidelines of the European Association of Cardiovascular Imaging (EACVI) [20].24-h ECG ambulatory Holter monitoring: Study participants wore a 24-h ECG ambulatory Holter monitor to record continuous ECG data. Key measures included the total burden of premature atrial and ventricular contractions, episodes of AF, microvolt T-wave alternans (TWA), heart-rate variability (HRV) indices, and deceleration capacity.Plasma biomarkers: Blood samples were collected at baseline and stored at −80 °C for subsequent biochemical analysis. The plasma biomarkers to be measured include galectin-3, homocysteine, high-sensitivity cardiac troponin I (hs-cTnI), procalcitonin, and brain natriuretic peptide (BNP).
